## 3. Discussion

This multicenter, randomized, double-blind study represents a pioneering effort to evaluate the efficacy of house-centered VRFT in individuals with SCI released from medical care with a physician’s recommendation in South Korea. Optimal SCI care recommends that rehabilitation be administered in the individuals’ residences or local environments according to the specific requirements and choices [40]. Rehabilitation exercises performed at home are enabled through VRFT, an innovative modality [41]. VRFT platforms are compact, easy to use, and allow clinicians to monitor them remotely, making them particularly suited for use at home [42]. VRFT conducted at home is appropriate for individuals with SCI released from intensive hospital treatment and seeking to restore their regular functions. Following hospital-based rehabilitation, this is crucial for individuals with advanced SCI to either sustain or intensify their therapy regimen. VRFT acts as an adjunct therapy to conventional face-to-face rehabilitation, usually taking place one to three times weekly. This approach enables the continuation of therapeutic exercises after formal rehabilitation has concluded. Prior research indicates that an increase of at least 15 h in rehabilitative exercise is necessary to significantly improve post-SCI functional recovery [43]. Individuals with SCI might find it simpler to meet the necessary physical activity requirements if they have the flexibility to carry out daily workouts at home according to their own plan.

VRFT conducted at home has the capability to increase workout intensity, promote rehabilitation, and enhance conditioning. Our research serves as an initial step towards validating this hypothesis. To date, only a limited number of small randomized controlled trials have investigated VRFT in a residential environment. The previous study utilized a motion-sensing exercise regimen conducted three times a week in a domestic setting, supplemented by twice-weekly clinic visits [44]. This research will utilize a VRFT platform offering a diverse array of exercises, thereby enabling enhanced personalization to achieve the specific therapeutic objectives of SCI patients. Moreover, the VRFT outlined in this study will be conducted completely within the home environment.

We expect that VRFT will be deemed practical, given that the devices can be easily set up in participants’ residences and that individuals can efficiently master and advance with VRFT. Additionally, it is anticipated that individuals will find VRFT enjoyable and appreciate its advantages in their rehabilitation journey, avoiding negative outcomes like accidents or mishaps.

The results from this study will offer a framework for individuals with SCI to securely engage in VRFT and workout at home after hospital-based rehabilitation. Our plan is to present our results in academic publications and share them at symposia, distributing the information through meetings focused on SCI rehabilitation.

It is essential to recognize that this study will have limitations due to the small number of participants, with just 15 individuals assigned per exercise group. Undertaking a pilot study is a sensible initial step before investing substantial resources in the study; however, the limited sample size might restrict our capacity to identify meaningful variations among the groups. Following studies, our study plans to undertake an extensive study to assess the impact of VRFT conducted at home on physical outcomes, including muscle function, cardiopulmonary fitness, body composition, and functional abilities. The findings will guide future studies by providing insights into aspects such as physical measurements, sample size, VRFT duration, weekly frequency, exercise intensity, time, and type of interventions. Practical insights into home-based VRFT post-hospital discharge are essential for guiding future study endeavors. Our study focuses on how hospital-based professionals and fitness trainers can work together to facilitate the implementation of VRFT for individuals with SCI after their hospital discharge. We aim to make substantial progress in this area over the next few years. The increasing adoption of technology in home-based settings positions VRFT as a promising method to enhance rehabilitation intensity and improve health conditions for those recuperating for individuals with SCI.

## 4. Conclusions

This study is poised to provide novel insights into the efficacy of VRFT programs for individuals with SCI, facilitating their safe engagement in home-based VRFT under the supervision of a healthcare professional post-discharge. We also seek to explore the feasibility of home-based exercise for SCI patients following their discharge from the hospital. Additionally, should this innovative exercise training method demonstrate effectiveness, it could generate significant data to inform the creation of more thorough rehabilitation programs for individuals with SCI moving forward. Additionally, should this innovative exercise training method demonstrate effectiveness, it could generate significant data to inform the creation of more thorough rehabilitation programs for individuals with SCI moving forward.

## Figures and Tables

**Figure 1 life-14-00859-f001:**
[figure not shown]
Flowchart. NRH, National Rehabilitation Hospital; NRC, National Rehabilitation Center; BSH, Bucheon SM Hospital; BSSC, Bucheon SM Sports Center; NHISHI, Korea National Health Insurance Service Hospital in Ilsan; RCG, Rehabilitation–sports Center in Goyang; KUHA, Korea University Hospital in Anam; GPC, Good Playground Center.

**Figure 2 life-14-00859-f002:**
[figure not shown]
Intervention program. (**a**) Experimental group—participant interacting with a virtual reality fitness training apparatus. (**b**) Experimental group—home-based use of the virtual reality fitness training system.

**Table 1 life-14-00859-t001:** Intervention protocol.

Warm-Up/Cool-Down		Upper Extremities	Trunk
Aerobic	Flexibility		
Freewheeling	- Static stretching - Dynamic stretching	- Back press - Overhead press - Front press - Bow pull - Shoulder press - Triceps kickback - Overhead arm-twist - Overhead arm spin	- Overhead side bend - Overhead twist - Pendulum bend - Overhead bend - Seated forward press - Seated twist - Russian twist - Seated ring raise - Ring raise combo - Fan pose - Warrior pose - Standing forward fold - Hinge pose

**Table 2 life-14-00859-t002:** Collection of data: medical information and anthropometric measurement part data.

Medical Part	Age	Years
	Gender	Male or female
	American Spinal Injury Association (ASIA) level	A, B, C, D, E
	Hypertension, anemia, dyspnea or asthma, orthostatic hypotension, diabetes, medications for heart disease, coronary stent, epilepsy, medications for anticoagulants, medications for depression, rigidity, autonomic dysreflexia, bladder management, bowel care, pressure ulcer, acute low back pain within 4 weeks, joint pain, medications for osteoporosis, hip or femur fractures	Yes or no
Anthropometric Part	Blood pressure	mmHg
	Height	cm
	Weight	kg
	Body mass index	Underweight/normal weight/overweight
	Days of discharge from the hospital	Number of days

**Table 3 life-14-00859-t003:** Duration of study: timeline for enrollment, interventions, and assessments in this study.

Study Period				
	Enrollment	Allocation	Post-Allocation	Closeout
Timepoint, baseline	t	0	T16	tx
Enrollment				
Eligibility screening	X			
Informed consent	X			
(Participant) Self-report questionnaires	X			
(Clinicians) Confirm participants’ self-report questionnaires and medical history and write doctor’s notes	X			
Allocation		X		
Assessments				
Baseline variables		X		
Post-intervention variables			X	X
Intervention				
Experimental group			X	X

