### 2.2. Participants

Participants may be eligible for the study if they (1) have been diagnosed with SCI, (2) have completed their initial hospitalization and rehabilitation, and are now living in the community, and (3) have provided informed consent and are willing to participate in this research. To address ethical concerns, all participants, including those in the control group, will continue to receive standard care and support as per clinical guidelines. Those requiring immediate or additional rehabilitation will not be excluded from receiving necessary interventions outside the scope of the study. Participants will not be eligible for the study if they (1) are presently receiving inpatient care, (2) cannot participate in exercise activities because of other nervous system disorders (apart from SCI), lower limb orthopedic issues, or severe cardiovascular or respiratory conditions, and (3) are assessed by the evaluator as unable to perform the required tasks.

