### 2.3. Randomization

Following the acquisition of informed consent from the participants, each team supervisor will identify and refer suitable candidates for the study. Subsequently, an independent statistician, not affiliated with the study team, will conduct the randomization process. Within each institution, participants will be categorized into two distinct subgroups through a block randomization approach. By employing blocks of size two in each stratum, an equal distribution ratio of 1:1 between the experimental and control groups will be achieved.

The randomization schedule will be generated utilizing SPSS software version 23.0 (IBM Corp., Armonk, NY, USA). The statistician responsible for the randomization will determine the block size and seed number through a random selection process. Thereafter, the randomized allocations will be sealed in packets, each designated for a participant, and delivered to the manager when the trial begins.

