### 2.7. Measures

Individuals with SCI will perform initial assessments and subsequent evaluations after 16 classes, utilizing the assessment outlined (Table 2). A custom-designed questionnaire will be used to gather descriptive and sociodemographic information. Outcomes will measure muscle function (including grip strength), cardiopulmonary fitness (including VO_2_peak and respiratory function), body composition (through full-body DXA scanning and bioimpedance measurement), and physical performance (functional reach test) to determine overall physical fitness. The primary outcome of this study is physical fitness factors, specifically muscle strength, cardiopulmonary fitness, body composition, and physical performance. Secondary outcomes include psychological factors such as quality of life. Individuals with SCI will perform initial assessments and subsequent evaluations after 16 classes utilizing the assessment outlined in Table 2. Incorporating these spinal cord injury-specific measures will provide a thorough evaluation of the participants’ rehabilitation progress and functional gains following the training.

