### 2.9. Data Collection Methods and Analysis

Outcome measures will be collected before and after the 16 intervention sessions, excluding the sociodemographic and descriptive information.

The sample size determination was based on prior research findings [34]. A power analysis was conducted using G*Power software (version 3.1.2.) [39]. The analysis used an effect size of 0.5 for the outcomes, a power level of 80% (type II error of 0.2), and a significance level of 0.05. We calculated that 29 individuals per group would be required to achieve the necessary statistical power. Therefore, we plan to enroll 30 individuals per group, resulting in a total of 120 participants across the four groups. This calculation ensures sufficient power to detect meaningful differences between the intervention and control groups.

We will assess participant characteristics and baseline comparisons to assess the comparability between the exercise and control groups. A table will be provided to display the characteristics of individuals assigned by the group. Percentages and frequencies will be used to present categorical elements, and time intervals along with continuous elements will be summarized using medians, standard deviations, means, and interquartile ranges. This procedure secures the baseline equivalence between the groups.

An intention-to-treat framework will be employed for our statistical analysis. Kolmogorov–Smirnov analysis will be used to assess the normality of the dependent variables for the outcomes. The responsible variables will be characterized based on their distribution, utilizing either medians and interquartile ranges or means and standard deviations. To achieve the objective, hypothesis tests will be conducted for each outcome, positing that the exercise group will have superior outcomes compared to the control group. All estimates will be accompanied by intervals with 95% confidence level. Student’s *t*-test will be applied for independent samples that follow a normal distribution, while the Mann–Whitney U test will be utilized for data that do not conform to a normal distribution.

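### Table 2's ASIA item is an A–E impairment grade, and the table lists no neurological level or date of injury; adding both and adjusting for level would be a cheap gain

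*Protocol article*

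**What the plan says.** Table 2 is captioned "Collection of data: medical information and anthropometric measurement part data" and is the only itemised list of baseline characteristics in the article. Its injury descriptor is "American Spinal Injury Association (ASIA) level", with the values A, B, C, D and E. The table also lists age, gender, 19 yes/no medical items, blood pressure, height, weight, body mass index and days since discharge.

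Section 2.2 admits people who "have been diagnosed with SCI", have finished initial hospitalisation and rehabilitation, and consent. It states no criterion on level. One exclusion covers people whom the evaluator judges unable to do the required tasks.

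Section 2.3 stratifies by centre: "Within each institution, participants will be categorized into two distinct subgroups through a block randomization approach". Section 2.7 makes physical fitness factors the primary outcome and lists "muscle function (including grip strength), cardiopulmonary fitness (including VO_2_peak and respiratory function", along with body composition and the functional reach test. Section 2.9 compares the arms with Student's t-test or the Mann–Whitney test and names no covariate. Of the baseline table it says: "This procedure secures the baseline equivalence between the groups".

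Two other baseline sources are mentioned, and the content of neither is shown. Section 2.7 states: "A custom-designed questionnaire will be used to gather descriptive and sociodemographic information". Table 3 has clinicians confirm the self-report questionnaires "and medical history and write doctor’s notes".

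**The concern.** The label and the values do not agree. A reader who sees the word level will assume that the site of the lesion is captured, but the values allow only a grade. A participant with a grade A cervical lesion and one with a grade A lumbar lesion have the same entry.

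That matters because of the endpoints chosen. Where the lesion lies decides whether the hands, arms, trunk and breathing muscles are affected, and those muscles produce grip strength, arm-crank VO2peak, spirometry, MIP/MEP and seated reach. The training itself uses a hand-held ring and exercises for the upper extremities and trunk (Section 2.6 and Table 1), so response could also vary with level.

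Three things are at stake. A chance imbalance in level would not show in the table of characteristics. It could not be adjusted for from the listed variables. Variation between levels would stay in the error term of an unadjusted test, and readers could not tell which patients the result applies to.

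**Working it through.** **Reading the documents.** The article was read for any variable that could encode level: eligibility (2.2), stratification (2.3), enrolment procedures (2.5), measures (2.7), analysis (2.9) and Tables 2 and 3. None names a cord segment, tetraplegia versus paraplegia, or date of injury. Days since discharge is not time since injury. The plan gives no figure of its own on this point, so there is none to reproduce.

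**Inputs for the illustration**
- Arm size: 60, from 120 participants allocated 1:1 (Sections 2.3 and 2.9).
- Cervical share p: 30% to 50%. This is an assumption; the documents give no figure.
- Gap δ between cervical and lower lesions in an endpoint, in within-level SD: 0.5 to 1.5. This is also an assumption.

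**1. Chance of imbalance.** Let X and Y be independent Binomial(60, p) counts of cervical lesions in the two arms. Ten percentage points is 6 patients and 15 points is 9 patients.

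| p | P(\|X − Y\| ≥ 6) | P(\|X − Y\| ≥ 9) |
|---|---|---|
| 0.3 | 0.273 | 0.090 |
| 0.5 | 0.315 | 0.120 |

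Section 2.9 speaks of 30 per group and four groups. If an arm were only 30, the chance of at least 10 points would be 0.481 to 0.519. The calculation ignores stratification by institution, which would lower these chances somewhat if the cervical share differs between centres.

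**2. Shift in an unadjusted comparison of post-treatment values.** Shift = imbalance × δ. At 10 points this is 0.10 × 0.5 = 0.05 up to 0.10 × 1.5 = 0.15 within-level SD.

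**3. Variance added by level.** Ratio of total to within-level variance = 1 + p(1 − p)δ². At p = 0.5 this is 1 + δ²/4:
- δ = 0.5: 1.06
- δ = 1.0: 1.25
- δ = 1.5: 1.56

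**4. Scale against the planned effect.** Section 2.9 uses an effect size of 0.5. If that is in total SD units, the shift at p = 0.5 is 0.05/√1.0625 = 0.05 up to 0.15/√1.5625 = 0.12, or about a tenth to a quarter of the planned effect.

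**The case against.** A reader might infer that the trial does not record level of injury at all. The documents do not support that. The questionnaire and the clinician-confirmed history are not shown, the article condenses a fuller protocol, and level may well be in those notes. What can be said is that Table 2 lists no such field and that its ASIA item does not supply one. Level held only in free notes is still not a study variable to be tabulated or adjusted for.

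A reader might also infer that nothing balances level, or that comparability cannot be shown. Neither follows. Randomisation balances level in expectation, and the nominal type I error already allows for chance imbalance. The endpoints are themselves measured before randomisation (Section 2.5), so each arm's starting values can be compared. Adjusting for those values would remove part of any shift. Section 2.9, however, names no such adjustment and does not say whether post or change values are tested.

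The exclusion for inability to perform the tasks may narrow the range of upper-limb function, by an unknown amount; it does not record level. Nor do the documents rank level as the strongest determinant of these endpoints. The point needs only that they depend on the muscles concerned.

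Finally, covariates are often left to a statistical analysis plan, which is not shown here. That limits the complaint about the analysis. It does not touch the mislabelled item, which is an error in the printed text.

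**Conclusion.** The point holds as a cheap improvement, not as a flaw that invalidates the comparison. It is certain from the text that the ASIA item is mislabelled, that level and date of injury are missing from the one itemised baseline list, and that the comparison as described is unadjusted.

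The size is hypothetical. The 27% to 32% chance of a 10-point imbalance, and the shift of 0.05 to 0.15 within-level SD at 10 points, rest on an assumed cervical share, an assumed gap, 60 per arm and unadjusted post values. They show that recording level is worthwhile; they do not show that this trial will be biased.

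The sentence on baseline equivalence in Section 2.9 overstates what a table can do. It would need rewording even if level were listed, since a table describes the arms and secures nothing.

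**What to change.** - In Table 2, rename the A–E item as impairment grade.
- Add neurological level (at least cervical, thoracic, or lumbar and below) and date of injury as study variables, taken from the medical history that clinicians already confirm at enrolment (Table 3). If the questionnaire or notes already hold them, say so and list them.
- Report both by arm in the table of characteristics.
- In Section 2.9, prespecify level and the endpoint's baseline value as covariates in the between-arm comparison.
- Replace the sentence on baseline equivalence with one saying that the table describes the arms at baseline.
- Results by cervical versus lower level are optional and should be labelled descriptive.

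The cost is two extra data fields from existing history and one more covariate. No new test or visit is needed.

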## Data Availability

The authors will make the data available upon reasonable request.
